**Methods: monitoring**			
Data monitoring	21a	Composition of data monitoring committee (DMC); summary of its role and reporting structure; statement of whether it is independent from the sponsor and competing interests; and reference to where further details about its charter can be found, if not in the protocol. Alternatively, an explanation of why a DMC is not needed	Yes
	21b	Description of any interim analyses and stopping guidelines, including who will have access to these interim results and make the final decision to terminate the trial	Yes
Harms	22	Plans for collecting, assessing, reporting, and managing solicited and spontaneously reported adverse events and other unintended effects of trial interventions or trial conduct	Yes
Auditing	23	Frequency and procedures for auditing trial conduct, if any, and whether the process will be independent from investigators and the sponsor	Yes
**Ethics and dissemination**			
Research ethics approval	24	Plans for seeking research ethics committee/institutional review board (REC/IRB) approval	Yes
Protocol amendments	25	Plans for communicating important protocol modifications (eg, changes to eligibility criteria, outcomes, analyses) to relevant parties (eg, investigators, REC/IRBs, trial participants, trial registries, journals, regulators)	Yes
Consent or assent	26a	Who will obtain informed consent or assent from potential trial participants or authorized surrogates, and how (see Item 32)	Yes
	26b	Additional consent provisions for collection and use of participant data and biological specimens in ancillary studies, if applicable	Yes
Confidentiality	27	How personal information about potential and enrolled participants will be collected, shared, and maintained in order to protect confidentiality before, during, and after the trial	Yes
Declaration of interests	28	Financial and other competing interests for principal investigators for the overall trial and each study site	Yes
Access to data	29	Statement of who will have access to the final trial dataset, and disclosure of contractual agreements that limit such access for investigators	Yes
Ancillary and post-trial care	30	Provisions, if any, for ancillary and post-trial care, and for compensation to those who suffer harm from trial participation	Yes
Dissemination policy	31a	Plans for investigators and sponsor to communicate trial results to participants, healthcare professionals, the public, and other relevant groups (eg, via publication, reporting in results databases, or other data sharing arrangements), including any publication restrictions	Yes
	31b	Authorship eligibility guidelines and any intended use of professional writers	Yes
	31c	Plans, if any, for granting public access to the full protocol, participant-level dataset, and statistical code	Yes
**Appendices**			
Informed consent materials	32	Model consent form and other related documentation given to participants and authorized surrogates	Yes
Biological specimens	33	Plans for collection, laboratory evaluation, and storage of biological specimens for genetic or molecular analysis in the current trial and for future use in ancillary studies, if applicable	Not applicable

* *It is strongly recommended that this checklist be read in conjunction with the SPIRIT 2013 Explanation and Elaboration for important clarification on the items. Amendments to the protocol should be tracked and dated. The SPIRIT checklist is copyrighted by the SPIRIT Group under the Creative Commons “Attribution-NonCommercial-NoDerivs 3.0 Unported” license*.

### Study Design and Setting

This randomized, controlled clinical trial is carried out at the Hangzhou Hospital of Traditional Chinese Medicine Affiliated to Zhejiang Chinese Medical University, Hangzhou, China (Figure 1).

**Figure 1 F1:**
[figure not shown]
Flow chart of the study design.

### Sample Size

According to previous similar reports (13), the average value of IRD in the physical training group was 2.09 after treatment, and the average value of IRD in the acupuncture and physical training group was expected to be 1.43 after treatment in this study. Three groups were set up in this study. The test level was α = 0.05, the test efficiency was 1–*β* = 0.90, and the two-sided test was conducted. The sample size was estimated by PASS15.0 software (13), effectiveness size is 0.313249. Considering 2-sided *P*-values to be deemed statistically significant at *P* < 0 0.05 and a power of 90%, 43 participants would be required per group (nQuery Advisor, version 4.0; Statistical Solutions). Estimating that 10% of patients might be lost to follow-up, we planned to enroll a total of 144 participants, with 48 in each group.

### Participants and Recruitment

The study was conducted from March 2022 to March 2023. The acupuncture group received acupuncture and physical training (*n* = 48), the sham acupuncture group received sham acupuncture and physical training (*n* = 48), and the physical training group received physical training (*n* = 48).

Participants were recruited from inclusion criteria:

(1) A female aged 18–45 years with no previous history of pathological rectus abdominal dissection;(2) Vaginal delivery, 42 days to 1 year post-partum;(3) DRA diagnostic criteria:The patient should keep in the supine position, with knees bending about 90°, the whole body relaxed, and the soles of the feet flat. The examiner shall put the abdomen of one hand finger on the umbilical level of the patient;The patient is told to breathe through the abdomen and to lift one's head and shoulders slightly off the bed;

Measuring the width of the finger inserted by the examiner, DRA is diagnosed when IRD ≥ 2 cm (14–16).

(4) No cognitive barriers, able to understand and communicate correctly;(5) Have not received treatment for DRA in other hospitals or institutions;(6) Those who sign the informed consent cooperate with the treatment and can adhere to the completion of all treatment as planned.

Patients who meet the above six criteria can be included in this study.

The subjects studied for DRA in post-partum women should follow the following exclusion criteria:

(1) One is suspected or diagnosed with severe spinal lesions (such as spinal fractures, metastases, inflammatory or infectious diseases, cauda equina syndrome/widespread neurological disease) and neurological injury;(2) One has motor contraindications or severe infectious diseases such as fractures, severe heart disease, hypertension, cancer;(3) Any plans for surgery soon;(4) History of cesarean section;(5) Abdominal operation history;(6) Any of the above shall be excluded.

### Randomization and Binding

A total of 144 eligible patients were recruited and randomly assigned at a 1:1:1 ratio to receive acupuncture treatment or sham acupuncture treatment or be placed on a physical training. Central randomization, using an online or messaging system, was performed by the Brightech Magnsoft Data Services. The randomization sequence was generated in blocks of varying sizes and stratified by centers.

The acupuncture and sham acupuncture groups were blinded, while those in the physical training group were not. All clinical examinations were performed by [name] and [name] physiotherapists blinded to data collected through the questionnaire. Due to iodophor disinfection traces in the abdomen after electroacupuncture, the therapists knew the groups, so [name] performed electroacupuncture treatment after rehabilitation exercise first. All the therapists did not know the purpose of the experiment.

The acupuncture and sham acupuncture groups were blinded, while those in the physical training group were not. All clinical examinations were performed by [name] and [name], two physiotherapists blinded to data collected. Due to iodophor disinfection traces in the abdomen after electroacupuncture, the therapists knew the groups. So [name] performed electroacupuncture treatment after rehabilitation exercise first. Outcome assessors, data collectors, and statisticians did not know the purpose of the experiment and were blinded to the treatment allocation.

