## Abstract

**Background:** Diastasis rectus abdominis (DRA) is one of the common complications during pregnancy and post-partum, which has psychological and physical effects on post-partum women. Acupuncture, a worldwide alternative therapy, has attracted wide attention in preventing and treating diseases related to pregnancy and childbirth. This study aims to evaluate the efficacy of acupuncture combined with physical training in treating post-partum rectus muscle dissociation.

**Methods:** This is a randomized, controlled trial of DRA in post-partum conducted at Hangzhou Hospital of Traditional Chinese Medicine Affiliated with Zhejiang University of Chinese Medicine. The primary purpose is to evaluate the effectiveness of acupuncture and physical training on DRA in post-partum women. The study will be conducted from March 2022 to March 2023. The acupuncture group received acupuncture and physical training (*n* = 48), the sham acupuncture group received sham acupuncture and physical training (*n* = 48), and the physical training group received physical training (*n* = 48). These experiments perform once/day, five times a week for 2 weeks, followed up for half a year after the end of the course of treatment. Our tests perform a course of treatment, which includes a total of 10 consecutive treatments. Furthermore, the patient will be followed up for half a year after the treatment. Primary and secondary indicators, including inter recti distance (IRD), linea alba (LA) tension, the MOS item short-form health survey (SF-36), short-form McGill pain questionnaire-2 (SF-MPQ-2), body mass index (BMI), waist-to-hip ratio (WHR), leeds dyspepsia questionnaire (LDQ), menstrual distress questionnaire (MDQ), 10 items of edinburgh post-natal depression scale (EPDS-10), the modified body self-image scale (MBIS), international consultation incontinence questionnaire short-form (ICIQ-SF) and hernia-related quality-of-life survey (HerQles), which will be evaluated before and after treatment and half a year after treatment. Adverse events and side effects during each treatment will be collected and recorded.

**Discussion:** There is evidence that acupuncture and physical training can treat DRA in post-partum. In this study, we evaluate the effectiveness of acupuncture in post-partum with DRA.

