### Adverse Events Reporting and Safety Monitoring

Safety: Adverse events (AE), side effectiveness (SE) such as falls, joint sprains will be recorded during the evaluation.

Compliance: Incomplete information and number of shedding for the two selected cases were recorded during and after the evaluation.

Acupuncture and exercise training were used as intervention items in this study. Before participating in the study, each subject underwent clinical diagnosis and contraindications, and detailed records were made during the treatment process. DURING THE EXPERIMENT, any AE, SE (fall, joint sprain, bleeding, post-stitch, needle blocking, etc.) will be recorded in detail and reported to the project leader. Subjects with adverse events will be treated in the hospital where the project is being implemented, and the project team will bear the treatment and examination costs.

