### Data Analysis

Based on Preliminary experiment results, we estimated that each of the three clinical researchers involved in the trial would recruit around 28 patients in 3 months. In order to retain most of the patients during follow-up, we gather the patients into a WeChat chatting group to answer their questions anytime. Moreover, actively cooperate with their appointment time. We expect the loss to follow-up to be below 10%.

Baseline characteristics and clinical outcomes are described based on the intention-to-treat population (*n* = 144). Continuous variables are presented as mean (SD), and categorical variables are described as number and percentage.

The principal analysis for primary and secondary outcomes will be a generalized linear model (GLM) including the intervention arm, the dependent variable's baseline score, and other variables imbalanced at baseline as covariates. The dependent variable will be the post-intervention score. The GLM does not need a normal distribution in the dependent variable. However, the distribution of the variables will be analyzed using de Shapiro- Wilk test to perform an adequate descriptive analysis. The choice of the link function will depend on the distribution of the variable.

Other variables will be added as confounders in the model as secondary sensitivity analyses. We will first fit separate models, including each confounder, one at a time. Those variables whose inclusion in the model changes the estimates' treatment effectiveness by at least 10% will be considered as confounders. As suggested in the CONSORT statement, decisions about confounders will not be based on *P*-value.

Missing data of withdrawn participants will be accommodated with multiple imputation procedures in Stata 25.0 software (Stata Corporation). All *P*-values were from 2-sided tests, and results were deemed statistically significant at *P* < 0.05.

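### Randomisation is described as stratified by centre in a one-hospital trial, so it is plain permuted blocks with no prognostic factor balanced by design; the gain from correcting this is modest and lies mainly in time since delivery

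*Protocol article*

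**What the plan says.** Randomization and Binding describes central randomisation of 144 women at 1:1:1 and states: "The randomization sequence was generated in blocks of varying sizes and stratified by centers". No other stratification factor is named.

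The rest of the article describes one site:

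- Abstract: "This is a randomized, controlled trial of DRA in post-partum conducted at Hangzhou Hospital of Traditional Chinese Medicine".
- Study Design and Setting: "This randomized, controlled clinical trial is carried out at the Hangzhou Hospital of Traditional Chinese Medicine".
- Adverse Events Reporting and Safety Monitoring uses the singular: women with adverse events are to be "treated in the hospital where the project is being implemented".

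Data Analysis expects that "each of the three clinical researchers involved in the trial would recruit around 28 patients in 3 months", but does not call these researchers centres or place them at different hospitals.

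On the entry range, Participants and Recruitment requires "Vaginal delivery, 42 days to 1 year post-partum". On the analysis, Data Analysis specifies a generalised linear model (GLM) with arm, the baseline value of the outcome, and any other variables found imbalanced at baseline. Further variables may be added one at a time in sensitivity analyses, and count as confounders if they move the treatment estimate by at least 10%.

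**The concern.** Stratifying by centre has an effect only where there are at least two centres. With one hospital, the sentence on stratification and the sentences on setting cannot both describe the design. Either the stratification is empty, or there are sites the article does not mention, or another factor was used and is misnamed. This is a positive statement about how allocation works, not a detail that an article leaves to a fuller document.

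At stake is a reader's belief that the allocation was restricted on something that matters. Entry covers 42 days to 1 year after delivery, a period in which the Background reports falling frequency of diastasis: 39–45% of women at 6 months and 23–32% at 1 year. Stage of natural recovery is therefore a plausible prognostic factor. It is known before allocation, yet it is neither a stratum nor a named covariate.

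**Working it through.** **1. What the stated scheme does.** Number of strata = number of centres = 1. Permuted blocks within one stratum keep the arm totals close and, through the blocks, spread the arms over calendar time. They restrict no patient characteristic.

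**2. The plan's own sample size.** Inputs from Sample Size: α 0.05 two-sided, power 0.90, three groups, effect size 0.313249. The article does not name the metric; it is read here as Cohen's f. One-way ANOVA with noncentrality 3n × 0.313249² gives power 0.893 at n = 43, 0.89999 at n = 44 and 0.907 at n = 45. The stated 43 is reproduced to within two women per arm. Loss to follow-up: 43 / 0.9 = 47.8, so 48; 3 × 48 = 144. Stratification enters none of these steps, so the figures stand whichever way the contradiction is resolved.

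**3. Chance difference in time since delivery (assumption: entry uniform from 42 days to 12 months).**

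- 42 days ≈ 1.38 months; range = 12 − 1.38 = 10.62 months.
- SD = 10.62 / √12 = 3.07 months.
- SE of the difference between two arms = 3.07 × √(2/48) = 0.63 months.
- 95% range = ±1.96 × 0.63 ≈ ±1.2 months.

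**4. As a two-level factor.** Under the same assumption, (6 − 1.38) / 10.62 = 44% of women would be at or below 6 months, close to an even split. For an even split at 48 per arm, two given arms differ by 8 or more women in about 13% of trials, and some pair of the three does so in about 28%. With the factor as a stratum, arms can differ within a level only by what one unfinished block allows. The block sizes are not given, so that limit cannot be stated as a number.

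**5. On a standardised scale, for any factor not stratified.** SE = √(2/48) = 0.204. A difference above 0.25 SD occurs in 22% of trials for a given pair and in 44% for at least one pair. Above 0.5 SD the figures are 1.4% and 3.8%.

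**6. What this could mean for IRD.** The documents give no slope of IRD on time since delivery, so the effect cannot be computed. It can be bounded by asking what slope would be needed. The planned difference is 2.09 − 1.43 = 0.66 (taken as cm). A shift of 1.2 months (1.23 before rounding) equals one tenth of that difference if IRD falls, given baseline IRD, by 0.066 / 1.23 = 0.054 cm per month. It equals the whole difference only at 0.66 / 1.23 = 0.54 cm per month.

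**7. A covariate already in the model.** For baseline IRD, a chance difference at its 95% limit is 1.96 × 0.204 = 0.40 SD. With linear adjustment and 144 − 3 = 141 within-arm degrees of freedom, the variance of a pairwise contrast rises by the factor 1 + (0.40² / 141) / (2/48) = 1.027, and the SE by about 1.4%. Stratifying on baseline IRD would therefore add little.

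**The case against.** The strongest reply is that only one word is wrong. Unstratified permuted blocks at 48 per arm are an accepted design, and the lack of a prognostic stratum is not in itself an error. Randomisation balances every factor in expectation. Chance imbalance is already reflected in the standard error and in the 5% level. All of this stands.

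A reader might infer from the empty stratification that no prognostic factor is balanced at all, or that the comparison is biased. The documents support neither: what is missing is balance by design, not balance in expectation. A reader might also infer that differences in entry severity go uncorrected. They do not, because the principal model contains baseline IRD. Nor is there ground to read the three recruiting researchers as centres, or to assume undisclosed sites.

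The prognostic argument also has limits. The 6-month and 1-year figures in the Background refer to post-partum women in general. They do not show that time since delivery predicts IRD among women selected for an IRD of at least 2 cm once baseline IRD is in the model, and natural recovery runs in all three arms. The ±1.2 months rests on an assumed entry distribution and does not convert to centimetres without a slope that the documents do not give.

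The model's provision for imbalanced variables could bring in time since delivery, and the 10% rule could do so in a sensitivity analysis. Both decisions are taken after the data are seen. The article gives no criterion for imbalance, though a separate analysis plan may.

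The contradiction remains, as does the modest case for fixing the handling of this one factor in advance.

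**Conclusion.** The point holds as a contradiction in the text with a modest design consequence. On the single-hospital description the allocation is plain permuted blocks, and the claimed stratification balances nothing. Alpha, sample size and the validity of the comparison are unchanged.

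The room for improvement lies mainly in time since delivery. The chance shift between two arms is about ±1.2 months if entry is uniform over the permitted range. It would reach a tenth of the planned IRD difference only if IRD depended on time by about 0.05 cm per month after allowing for baseline IRD, and that slope is unknown. The contradiction itself rests on no assumption; the size of the gain rests on the entry distribution and on that slope.

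**What to change.** Which change applies depends on whether the sequence is already in use. The article does not settle this: the randomisation section is in the past tense, while the Abstract speaks of a study still to be conducted.

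- **Allocation still open:** in Randomization and Binding, replace centre with one two-level factor known before allocation, time since delivery (for example up to 6 months or over 6 months; the cut is an assumption for the investigators to settle). Keep the varying blocks and the central system. In Data Analysis, enter the factor in the principal GLM whether or not it turns out imbalanced.
- **Sequence already in use:** do not rewrite the allocation as something it was not. Reconcile Randomization and Binding with the Abstract and Study Design and Setting by describing unstratified permuted blocks, or by naming the sites or the factor actually used. Prespecify time since delivery as a covariate in the principal GLM.

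The first route costs a small change to the central system's set-up and one model term. With two strata there can be two unfinished blocks, so arm totals may depart slightly from 48. The second route costs one corrected sentence and one model term. Neither changes the sample size.

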### Intervention

Acupuncture group: the patient was placed in the supine position, exposing the abdomen, and acupoints RN12 (Zhongwan), RN10 (Xiawan), ST25 (Tianshu), GB26 (Dai Mai), RN6 (Qi Hai), and RN4 (Guanyuan) were selected. The selection of acupoints was based on the previous literature and clinical experience of DRA. The skin at the acupoints was routinely disinfected, and the disposable sterile acupuncture needles were used for vertical acupuncture of 25–40 mm, 30 min once/day, five times a week for 2 weeks (Figure 2A).Sham acupuncture group: non-penetrating sham acupuncture is performed on the same points as the treatment group on the abdomen. Streitberger placebo needles with blunt tips are used. When they are fixed on the skin through plastic rings, patients will feel a pricking sensation, simulating a skin puncture. However, instead of penetrating the skin, the needles retract up into the shaft when pressed against the skin. We will formulate and follow standardize step-by-step instructions and operations to use the same rituals in the acupuncture and sham acupuncture groups as far as possible, 30 min once/day, five times a week for 2 weeks (Figure 2B).Physical training group: (1) Abdominal breathing: supine position, lower limb hip, and knee flexion, foam bricks are clamped between the legs. the abdomen will be humped while inhaling and is forced to the navel while exhaling. Abdominal muscles and pelvic floor muscles are forced to contract at the same time, ten times a group for three groups. (2) Left and right-side leg rotation: buckling, supine, legs down to the right. inhale, abdominal bulge, expiratory when abdomen muscle contraction, to, make double leg down to the left (power is core abdominal muscles, legs, not too much), the therapist skill on the right side of the internal, external oblique muscle in patients with muscle contraction, the muscle belly line direction, the other patients on your knees. Apply some resistance according to the patient's strength of the force. Do it alternately, 10 times on each side. (3) Stretch legs after stomach retraction: Patients prone position, the abdominal pad is a soft pillow, inhale, abdominal bulge, expiratory when abdomen muscle contraction (imagine navel carried from pillow side), in turn, the waist, on the left side of the hips, on the left side of the thigh, to raise the left lower limb, the core in the waist, leg without over pressure, and avoid the contralateral compensatory, therapists place the fourth finger near the lumbar spine feeling the relaxation from torn muscle contraction. Alternating left and right, do 10 reps on each side. (4) Ventral flat training: the patient is in the right described position, elbow flexion support on the bed surface, hip extension, calf flexion and thigh 90 degrees, abdominal uplift when inhaling, abdominal muscles when exhaling, upper body, buttocks and left lower limb straight lift off the bed surface, left upper limb lift, upper arm against the head, ear sticking, maintain relaxation after 10 s. Core in the abdomen, other parts of the body cannot apply excessive force. Alternating left and right, do 10 reps on each side (Figure 3).
